### Interventions

Patients with a hip fracture usually have surgery on the next available trauma operating list. Some patients may be delayed by medical factors such as anticoagulation, however, surgery will proceed as soon as is determined safe by the treating team. All patients will receive a general or regional anaesthetic. Routine prophylactic antibiotics will be given to all patients immediately before surgery and all patients will be assessed for venous thromboembolism prophylaxis according to local policy. At the end of the operation, a dressing is applied to the surgical wound. This trial will involve two types of wound dressing: standard dressing and NPWT.

#### Standard dressing

The standard dressing for a surgical wound comprises a non-adhesive layer applied directly to the wound that is covered by a sealed dressing. The standard dressing does not use ‘negative pressure’. The exact details of the dressing materials and duration will be left to the discretion of the treating surgeon as per their routine practice, but the details of each dressing applied in the trial will be recorded.

#### Negative-pressure wound therapy

The NPWT dressing uses an ‘open-cell’, solid foam layer which is laid onto the wound as an intrinsic part of a sealed dressing. A sealed tube connects the dressing to a built in mini-pump that creates a partial vacuum over the wound. This can only be kept on for 7 days according to the manufacturer that will be reflected in this study.

Any further wound dressing after the initial dressing will be recorded and will follow the allocated treatment unless otherwise clinically indicated.

### Outcome measures

#### Primary outcome

The primary outcome measure for this study is deep infection; We will use the CDC and Prevention definition of a ‘deep SSI’, that is a wound infection involving the tissues deep to the skin that occurs within 30 or 90 days of injury.^23^

The treating clinical team will make the diagnosis of ‘deep infection’, as per routine clinical practice. The treating clinicians will not be part of the research team. Since the prompt diagnosis and treatment of infection is fundamental to the patient’s routine clinical care, the treating surgeon/clinician will always document such a change in management in the patient’s medical record.

In addition to the rate of infection, time of diagnosis will be assessed; The CDC definition applies up to the 90 days after hip fracture surgery.^23^ However, the national care pathway for hip fractures involves remote follow-up at 4 months. Therefore, to ensure that assessment meets the CDC criteria and is consistent with existing care practice, each patient will be assessed at 30 days and 4 months.

At 30 days, the patient will be assessed either as an inpatient or over the telephone according to the relevant clinical parameters.

At 4 months patients will be asked, via telephone interview, about any further symptoms of infection which may have emerged since the 30-day time point. Of the infections that are identified, we will establish when the diagnosis was made in the course of recovery.

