## Aims and objectives

We aim to conduct a feasibility trial of NPWT versus standard dressing following hip fracture surgery. It is intended to obtain a reliable estimate of the rate of SSIs in the target population. In addition, feasibility will be considered in terms of other aspects of the trial such as recruiting and randomising large numbers from individual sites within a relatively short time frame.

The primary objective is:

To quantify differences in the rate of ‘deep infection’—as defined by the Centre for Disease Control (CDC)—after hip fracture surgery in standard dressing and NPWT. Patients will be assessed at 30 days and 4 months. We will examine how many deep infections occur, and when the diagnosis is made.

Both ‘how many deep infections’ and ‘when they are diagnosed’ will be crucial to inform the design of a full-scale trial. Each time point addresses the requirements of the CDC, and the routine follow-up of patients in the current UK care pathway.

The secondary objectives are:To determine the number and nature of further surgical interventions related to the injury, in the first 4 months after the index procedure.To investigate which outcomes will be required to assess cost-effectiveness, of NPWT versus standard dressing for wounds associated with hip fracture surgery in a definitive trial.To determine recruitment rate and willingness to participate in the trial.To capture the core outcome set for hip fracture studies.

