### Sample size

The purpose of the proposed feasibility study is to determine the rate of deep SSI which in turn will inform the sample size for the definitive trial. We will recruit a sample of 464 participants; divided equally in each of the two study arms. This is based on the number of hip fractures treated at each of the recruiting centres and assuming a conservative recruitment of 50% of eligible patients. Four hundred and sixty-four is based on Wilson’s CI method at two-sided 95% significance level with 20% loss to follow-up). This will allow us to estimate the overall 30-day deep infection rate within 3%–5% depending on the actual rate.

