### Statistical analysis

Standard statistical summaries (eg, means, SDs, medians, IQR) will be reported for all discrete and continuous outcome measures. Baseline data (eg, age and gender) will be summarised to check comparability between treatment arms. This will only be shared with the Data Management Committee (DMC) in the first instance at the end of the feasibility study. No formal hypothesis testing will take place; as per the aim of this feasibility study, the analysis will report the deep infection rates overall and in the two treatment groups on an intention-to-treat basis at 30 days and 4 months postrecruitment.

Should this study demonstrate that a full-scale trial is feasible, the data from this feasibility study will be included in the final analysis of the definitive trial. This is contingent on the future definitive trial being sufficiently similar to this feasibility study. Baseline and follow-up outcome data will therefore not be released to the trial team unless the lack of feasibility is determined based on observed infection rate at the end of the feasibility study, or the definitive study cannot be conducted for other reasons (eg, lack of funding). Reporting of the study outcomes will be done accordingly to enable to use of the outcome data in a future definitive trial if such a study goes ahead.

Recruitment and retention rates will be reported through a consort diagram and so will inform the planning of a definitive trial with respects to sample size and the time points of measurements.

It seems likely that some data may not be available due to voluntary withdrawal of patients, lack of completion of individual data items or general loss to follow-up. In this hip fracture cohort, there is significant mortality at 30 days—6.7%.^1^ Where possible the reasons for missing data will be ascertained and reported. Although missing data is not expected to be a problem for this study, the nature and pattern of the missing data is important to understand for the full study, so will be carefully considered.

Reasons for ineligibility, non-compliance, withdrawal or other protocol violations will be stated and any patterns summarised.

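### The 4-month infection question looks back only to day 30, so an early deep infection in a patient missed at day 30 may be left out of the 4-month rate

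*Protocol article*

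**What the plan says.** All references are to the protocol article.

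- **Primary outcome, 4-month contact.** Patients are interviewed by telephone "about any further symptoms of infection which may have emerged since the 30-day time point". No other infection question is stated for this interview.
- **Primary outcome, day-30 contact.** "At 30 days, the patient will be assessed either as an inpatient or over the telephone according to the relevant clinical parameters". It is planned for every patient.
- **Primary outcome, who decides and how events are dated.** "The treating clinical team will make the diagnosis of ‘deep infection’, as per routine clinical practice", and "the treating surgeon/clinician will always document such a change in management in the patient’s medical record". On timing: "Of the infections that are identified, we will establish when the diagnosis was made in the course of recovery".
- **Aims and objectives.** The primary objective adds: "We will examine how many deep infections occur, and when the diagnosis is made". Further surgery is to be counted over the whole of the first 4 months.
- **Statistical analysis.** "the analysis will report the deep infection rates overall and in the two treatment groups on an intention-to-treat basis at 30 days and 4 months", both counted from recruitment.
- **Sample size.** The 464 patients rest on "Wilson’s CI method at two-sided 95% significance level with 20% loss to follow-up", and the target is the overall 30-day rate.
- **Follow-up.** Deep infection is also investigated at 4 months, so that every patient has been assessed for the 90-day period that the CDC definition requires. Nothing there limits this to the time after day 30. The site research associate records complications at 30 days or discharge, and again at 4 months by telephone interview. Review of medical records is stated for people who decline to give follow-up data but allow access to their records.

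**The concern.** A 4-month rate counted from recruitment needs each patient's infection status for the whole period from day 0. A question that starts at day 30 supplies only the second part. The first part must come from the day-30 assessment, and the sample size calculation expects some patients to be lost.

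Consider a patient with a deep infection on day 15 who is not reached at day 30 but answers the telephone at 4 months. The stated question does not ask about day 15. Unless something else reveals the infection, the patient can enter the 4-month rate as uninfected. The contact that could have filled the gap has then been made without filling it.

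At stake are the 4-month rate and the count and timing of infections, which the primary objective says will shape the definitive trial. Any such error goes one way, towards too few infections, and recruiting more patients would not reduce it. The article already names capture of infections across institutions and care pathways as its potential limitation.

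**Working it through.** **1. The plan's own figure.** With 20% loss, 371 / 0.8 = 463.75, which rounds up to the stated 464. For n = 371, the full width of the Wilson 95% interval is 3.0 percentage points at a true rate of 2%, 4.5 at 5%, 4.9 at 6% and 5.6 at 8%. Reading the stated 3%–5% as full width therefore roughly reproduces the plan. The article does not state the true rates it assumed.

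**2. Inputs.**

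- From the article: 464 patients, 20% loss, local audit infection rates of 5% and 8%, and 30-day mortality of 6.7%.
- Assumed: a share m = 10% to 20% not assessed at day 30 (the upper end borrows the 20% allowance), and a share r = 25% to 75% of those reached at 4 months.
- Also assumed: equal infection risk in missed and assessed patients, no recovery by any other route, and missed patients who are reached later scored as uninfected. Patients reached at neither contact are left out of the denominator.

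**3. Formula.** Early infections are those before day 30.

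Relative undercount of early infections = m·r / (1 − m + m·r)

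| m | r | Calculation | Relative undercount | Recorded if the true early rate is 5% |
|---|---|---|---|---|
| 0.10 | 0.25 | 0.025 / 0.925 | 2.7% | 4.86% |
| 0.10 | 0.75 | 0.075 / 0.975 | 7.7% | 4.62% |
| 0.20 | 0.25 | 0.05 / 0.85 | 5.9% | 4.71% |
| 0.20 | 0.50 | 0.10 / 0.90 | 11.1% | 4.44% |
| 0.20 | 0.75 | 0.15 / 0.95 | 15.8% | 4.21% |

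**4. In patients, for m = 0.20 and r = 0.50.**

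- Assessed at day 30: 464 × 0.8 = 371.2.
- Missed at day 30 but reached later: 464 × 0.2 × 0.5 = 46.4.
- True early infections at 5%: (371.2 + 46.4) × 0.05 = 20.88.
- Not recorded: 46.4 × 0.05 = 2.32.
- Recorded: 18.56 / 417.6 = 4.44%.

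At an 8% rate with r = 0.75, 464 × 0.2 × 0.75 = 69.6 patients are involved and 69.6 × 0.08 = 5.57 infections go unrecorded.

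**5. Effect of deaths.** If the 6.7% who die by day 30 are part of the 20%, the share of missed patients who can be reached later is at most (20 − 6.7) / 20 = 0.665. The upper limit becomes 0.133 / 0.933, about 14%.

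**6. The 30-day rate.** Missed patients are absent from both numerator and denominator: 18.56 / 371.2 = 5.0%. Under equal risk this rate has fewer patients behind it but is not biased.

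**The case against.** **The interview question is not the whole capture system.** The outcome is the treating team's documented diagnosis. The Follow-up section sets no lower time limit on its 4-month check for deep infection. All complications related to the index wound are recorded, as is further surgery over 4 months. A reader might infer that the early infection in a missed patient is certain to be counted at neither time point. The documents do not support that: any of these routes could catch it. They are only partial, though. The 4-month complications entry comes from the same telephone interview. A note in the medical record does not enter the trial by itself, and record review is stated only for the routine-data-only group. A patient interviewed at 4 months is not in that group.

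**The sentence is an article's summary, not the questionnaire.** The case report forms are left to the trial team and may be wider. That is possible, but the article does state a look-back, and it is narrower than its own Follow-up section.

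**The size is an upper bound.** No passage says that a patient missed at day 30 is scored as uninfected, and the article promises to consider missing data carefully. The shares reached later have no source. The percentages apply to early infections only, so later infections dilute them in the cumulative 4-month rate. The central shift of about 0.6 percentage points is small beside a planned interval about 4.5 points wide at a 5% rate. All of this stands.

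**A second gap might be inferred.** A patient with wound symptoms from day 26, undiagnosed at day 30 and diagnosed on day 36, has no symptoms that began after day 30. Read literally, the question passes this patient by. The case is weak: the symptoms could already be on file from day 30, and the plan dates infections by diagnosis. It is not included in the size.

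**Conclusion.** The point stands as a risk of under-ascertainment in the 4-month rate and in the count and timing of infections. It is not a demonstrated bias. The stated look-back does not match a rate counted from recruitment or the Follow-up section's aim of assessing every patient over 90 days, and it would not by itself recover an early infection in a patient missed at day 30.

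If no other route recovers these cases and the patients concerned are scored as uninfected, the relative undercount of early infections is at most about 3% to 16%, depending on the assumed shares. Deaths by day 30 and the other capture routes probably make it smaller, and full recovery by those routes would remove it.

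A reader might also infer that the 30-day rate, on which the sample size rests, is biased. Under equal risk it is not. Bias there would need a different infection risk in missed patients, which the article does not show.

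The change is worth making because it corrects a stated rule at little cost, not because the expected error is large.

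**What to change.** In the Primary outcome section:

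- Replace the 4-month question with one put to every participant, whether or not the day-30 assessment was completed: has any wound infection been diagnosed or treated since the hip operation, and on what date was it diagnosed?
- Assign each infection to the 30-day or 4-month count by its date of diagnosis, not by when symptoms began or at which contact it was reported.
- Use the 4-month answer to complete day-30 status for patients missed at day 30.

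Then align the Primary outcome and Follow-up sections, so that both say the 4-month contact covers the whole period since surgery.

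The cost is a reworded question and a date field on the existing 4-month form, with no extra contact, visit or staff. The downside is recall over 4 months instead of 3, and some duplicate reports to match against the day-30 form.

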#### Secondary outcome measures in this trial

##### Mortality

Qualitative work with patients who sustain hip fractures identified mortality as an important metric.^24^

##### EuroQol EQ-5D-5L

The EuroQol EQ-5D is a validated measure of health-related quality of life, consisting of a five-dimension health status classification system and a separate Visual Analogue Scale.^25^ Responses to the health status classification system will be converted into multiattribute utility (MAU) scores using tariffs currently under development for England.^26^ These MAU scores will be combined with survival data to generate Quality Adjusted Life Year (QALY) profiles for the purposes of the economic evaluation. The EQ-5D has been validated to be completed by a patient’s proxy in case of continues impaired capacity.

##### Complications

All complications and surgical interventions related to the index wound will be recorded.

##### Resource use

Will be monitored to help inform the economic analysis plan in the subsequent definitive trial. Cost data will be obtained from national databases or will be estimated in consultation with the hospital finance department. The cost consequences following discharge, including NHS costs and patients’ out-of-pocket expenses will be recorded via a short questionnaire, which will be administered at 4 months postinjury. This will be either by patient or consultee.^27^

##### Mobility

The ability to walk indoors and outdoors is rated very highly by patients. It has been included in a recommended ‘core outcome set’ for trials assessing interventions in hip fractures.

##### Residential status

Also captured on case report form (CRF). The residential status is also part of the core outcome set for hip fractures and NHFD dataset.^24^ It will be captured at baseline and at 4 months.

##### Recruitment rate

The rate of recruitment of potential participants, both in terms of eligibility and those who consent (or on whose behalf consent is provided) will be recorded.

##### Retention rate

The rate of retention through the study visits of participants will be recorded.

### Adverse event management

Adverse events (AEs) are defined as any untoward medical occurrence in a clinical trial subject and which do not necessarily have a causal relationship with the treatment. All AEs will be listed on the appropriate CRF for routine return to the ‘WHISH’ central office.

Some AEs are expected as part of the surgical interventions, and do not need to be reported immediately, provided they are recorded in the ‘Complications’ section of the CRFs and/or patient questionnaires. These events are: complications of anaesthesia or surgery (bleeding or damage to adjacent structures such as nerves, tendons and blood vessels, delayed unions/non-unions, further surgery to remove/replace metalwork, dislocation, wound dehiscence and thromboembolic events). All participants experiencing Significant Adverse Events (SAEs) will be followed up as per protocol until the end of the trial.

### Follow-up

Each patient will be assessed in the current UK national audit framework for hip fracture patients. This means they will contact by telephone 4 months after surgery. As per the feasibility aims of this study, we will also assess each patient at 30 days. This may be in person as an inpatient or over the telephone is the patient has been discharged.

The 4-month time point will collect the data required for the NHFD, health-related quality of life and the other components of the hip fracture core outcome set.^24^ We will also investigate deep infection at the 4-month time point to ensure that each patient has been assessed by 90 days which is required by the CDC.

Details of any late complications will be sent securely to the trial coordinating centre. Complications will be captured on the CRF by the site research associate and recorded on the CRFs at 30 days/discharge and at 4 months via telephone interview.

Where a personal consultee has agreed to the patient’s involvement, we will ask them for the follow-up data if the participant has permanently lost capacity to consent. Those patients or consultees who do not wish to provide follow-up data but agree to the study team reviewing their medical records, clinical reporting forms will be completed by the site and returned in the same manner. This is referred to as ‘routine data only’ option.

### Sample size

The purpose of the proposed feasibility study is to determine the rate of deep SSI which in turn will inform the sample size for the definitive trial. We will recruit a sample of 464 participants; divided equally in each of the two study arms. This is based on the number of hip fractures treated at each of the recruiting centres and assuming a conservative recruitment of 50% of eligible patients. Four hundred and sixty-four is based on Wilson’s CI method at two-sided 95% significance level with 20% loss to follow-up). This will allow us to estimate the overall 30-day deep infection rate within 3%–5% depending on the actual rate.

### Rehabilitation

Early full weight-bearing mobilisation is routine in all cases of hip fracture. Further details of the rehabilitation will be left to the discretion of the treating team as per usual clinical practice.

### Data management

The CRFs will be designed by the trial manager in conjunction with the trial management team. All electronic patient-identifiable information will be held on a secure, password-protected database at the Kadoorie Centre, accessible only to the research team. Paper forms with patient-identifiable information will be held in secure, locked filing cabinets within a restricted area. Patients will be identified by a code number only. Direct access to source data/documents will be required for trial-related monitoring and/or audit by the Sponsor, NHS Trust or regulatory authorities as required. All paper and electronic data will be retained for at least 5 years after completion of the trial.

### Statistical analysis

Standard statistical summaries (eg, means, SDs, medians, IQR) will be reported for all discrete and continuous outcome measures. Baseline data (eg, age and gender) will be summarised to check comparability between treatment arms. This will only be shared with the Data Management Committee (DMC) in the first instance at the end of the feasibility study. No formal hypothesis testing will take place; as per the aim of this feasibility study, the analysis will report the deep infection rates overall and in the two treatment groups on an intention-to-treat basis at 30 days and 4 months postrecruitment.

Should this study demonstrate that a full-scale trial is feasible, the data from this feasibility study will be included in the final analysis of the definitive trial. This is contingent on the future definitive trial being sufficiently similar to this feasibility study. Baseline and follow-up outcome data will therefore not be released to the trial team unless the lack of feasibility is determined based on observed infection rate at the end of the feasibility study, or the definitive study cannot be conducted for other reasons (eg, lack of funding). Reporting of the study outcomes will be done accordingly to enable to use of the outcome data in a future definitive trial if such a study goes ahead.

Recruitment and retention rates will be reported through a consort diagram and so will inform the planning of a definitive trial with respects to sample size and the time points of measurements.

It seems likely that some data may not be available due to voluntary withdrawal of patients, lack of completion of individual data items or general loss to follow-up. In this hip fracture cohort, there is significant mortality at 30 days—6.7%.^1^ Where possible the reasons for missing data will be ascertained and reported. Although missing data is not expected to be a problem for this study, the nature and pattern of the missing data is important to understand for the full study, so will be carefully considered.

Reasons for ineligibility, non-compliance, withdrawal or other protocol violations will be stated and any patterns summarised.

